**Figure 1. F1:**
[figure not shown]
Workflow of study participants from initial screening, through delivery of the graded exercise therapy and cognitive behavioral therapy interventions to subsequent follow-up. At the 6- and 12-month time points, participants will also be asked about adherence to exercise and cognitive behavioral therapy strategies. 5×STS: 5-times sit-to-stand test; 6MWT: 6-minute walk test; ANC: absolute neutrophil count; CDK4/6: cyclin-dependent kinase 4/6; CS: cultural sensitivity assessment items; CSQ: Client Satisfaction Questionnaire-8; ET: endocrine therapy; FACIT-F: Functional Assessment of Chronic Illness Therapy-Fatigue; FACT-G: Functional Assessment of Cancer Therapy–General; GLTPAQ: Godin-Shephard Leisure-Time Physical Activity Questionnaire; Hb: hemoglobin; HGS: handgrip strength; LVEF: left ventricular ejection fraction; MAS: Medication Adherence Scale.

Exercise therapy will consist of a self-supervised, individualized exercise program prescribed by the rehabilitation physician. This graded exercise program consists of both aerobic (eg, brisk walking and cycling) and resistance exercises, customized to the participant’s pre-existing medical conditions and preferences. Exercise will be prescribed in a graded manner across 3 phases, at weeks 0, 4, and 8 (Table 1). The Modified Borg Rating of Perceived Exertion scale will be introduced to the participant, where the desired intensity of exercises is moderate, with a Rating of Perceived Exertion of 4‐6.

**Table 1. T1:** Graded exercise program (3 phases).

Phase	Weeks	Aerobic exercises	Resistance exercises
1. Foundation	0-4	3 times per week, 20-25 min, low- to moderate-intensity (RPE^a^ 3‐5)	2 times per week, at least 3 exercises. 1-2 sets of 8-12 repetitions of each exercise
2. Build up	5-8	3-4 times per week, 30 min, moderate intensity (RPE 4‐6)	2-3 times per week, at least 5 exercises. 2-3 sets of 8-12 repetitions of each exercise
3. Strength and endurance	9-12	4 times per week, 35-45 min, moderate intensity (RPE 5‐6)	2-3 times per week, at least 7 exercises. 2-3 sets of 8-12 repetitions of each exercise

a RPE: rating of perceived exertion.

At the first video consultation session, the rehabilitation physician will go through the exercise booklet in detail with each participant. A study research assistant will conduct weekly phone calls to check on the participants’ adherence to and compliance with the prescribed exercises. Over the 3 subsequent follow-up video consultation sessions (weeks 4, 8, and 12), the rehabilitation physician will review the exercises with the participants and implement modifications, if necessary, based on feedback from the participants. The type of aerobic exercise and resistance exercise will be tailored to the participant’s preference and guided by the rehabilitation physician.

Adverse event monitoring for GET is conducted via the following three methods:

Weekly phone calls are made by the study coordinator to check for the onset of any new symptoms, distress, or adverse events. Participants are advised to stop the exercises if they experience excessive fatigue (score >7 on the One-Item Fatigue Scale) or develop new and/or unusual pain, chest discomfort, nausea, severe dyspnea, or palpitations while engaging in exercise.Monthly video consultations with rehabilitation physicians.An exercise diary with provisions for participants to record any adverse events.

Any adverse events are also reported to the clinical investigators in the study team for further follow-up and a decision to continue with the study.

The CBT intervention will be delivered by trained clinical psychologists or psychology trainees under the supervision of a clinical psychologist across four 1-hour intervention sessions, delivered in English via telehealth within 12 weeks. This intervention will have 4 major components that have been adapted from previous randomized controlled trials (RCTs) evaluating the use of CBT in managing fatigue in BC [13,16,17].

The session structure and outline are as follows:

Session 1: psychoeducation on CRF, establishing personalized value-driven goals, the use of a fatigue tracking diary, and relaxation training.Session 2: behavioral skills training for symptom management of fatigue through energy conservation, activity pacing, and goal setting. We will also have a time allowance to discuss related issues such as sleep disturbance, mood, and cognitive challenges.Session 3: psychoeducation on the cognitive behavioral perspective using the ABCD (A: activating event, B: beliefs, C: consequences, and D: dispute) model, followed by cognitive strategies to manage worries.Session 4: strategies to maximize social support and change dynamics within the family. Consequently, we will summarize the skills learned in the last 4 sessions.

The CBT intervention will be tailored for local use. For example, adaptation of materials for a low reading level, inclusion of minimal writing exercises, and the use of examples and discussions surrounding social roles that have been amended to fit the local context. Summaries of the information for each session will be provided for participants’ reference, and they will also be asked to practice the skills introduced in the intervention after each session. The first 10 to 20 minutes at the start of each session are allocated to check on participants’ welfare and review their application of previously taught skills. Participants who indicate high distress will be assessed for safety, triaged, and referred to another mental health care professional for additional support if appropriate. Feedback will be qualitatively obtained from participants at the end of the fourth session, and any technical difficulties will be documented in the relevant consultation notes if any challenges were observed during the session.

The administration of the sessions is protocolized using therapist manuals, and prior to commencing sessions, therapists receive standardized training. Therapists are recorded during the sessions, with the content compared against a checklist to ensure that all relevant points have been covered during each session. Therapists also complete a form to indicate any deviation from the protocol, such as participants declining a certain activity or a longer time being taken than usual due to technical glitches.

Outcome measures will be assessed at 4 time points as illustrated in Figure 1: baseline, 3 months (time point 1), 6 months (time point 2), and 12 months (time point 3). At baseline, demographic information will also be collected, including reproductive history, education, marital status, and employment history, using a questionnaire adapted from a previous multiethnic cohort phase 2 study in the Singaporean population [18]. Participants will be evaluated for their perception of self-efficacy, measured using the Exercise Self-Efficacy Scale [19], and will also be screened for depression and anxiety symptoms using the 10-item Center for Epidemiologic Studies Depression Scale [20,21] and the Generalized Anxiety Disorder-7 scale [22], respectively.

### Measures

#### Primary Endpoints

The primary acceptability endpoint is defined as the percentage of participants who score at least 24 (out of a maximum of 32) on the CSQ-8 survey at 3 months. The primary feasibility endpoint is defined as the percentage of participants who are adherent to their therapy sessions (attending at least 3 out of 4 sessions for GET and CBT each).

#### CSQ-8

The CSQ-8 is an 8-item questionnaire that was developed as a brief global measure of client satisfaction and was abbreviated from the longer 18-item version of CSQ-8 [23]. The CSQ-8 was shown to have excellent performance in comparison with the original CSQ-18 [24]. In this study, the CSQ-8 will be used, along with additional questions about whether the program helped participants to better understand the overall experience of BC, and which version of CBT materials the participants found useful. The CSQ-8 score ranges from 8 to 32, with higher scores indicating greater satisfaction.

#### Cultural Sensitivity

Cultural sensitivity, which is the perceived cultural relevance of the program to the participant’s individual culture, will be assessed using 4 items adapted from the Cultural Sensitivity Assessment Tool [25]. Participants will respond to each item on a 4-point scale (ranging from “strongly disagree” to “strongly agree”). Scores range from 4 to 16, with higher scores indicating greater satisfaction and cultural sensitivity. This measurement tool has been successfully used in prior Singapore-based studies [26-28].

#### Uptake and Adherence

Participant uptake will be assessed based on the percentage of randomized patients who attended at least 1 session of their allocated intervention and the percentage of randomized patients who completed their allocated intervention.

Participant adherence during the study intervention period will be assessed based on the number of sessions of their allocated intervention attended by the patients. To assess participant adherence during the follow-up period, the following questions will be used:

For adherence to GET: “In the past 3 months, how often did you do your exercises as prescribed?”For adherence to CBT: “In the past 3 months, how often did you use any of the CBT strategies to manage your fatigue?”

Participants will respond on a 5-point scale (5=“all of the time,” 100%; 4=“nearly all of the time,” 90%; 3=“most of the time,” 75%; 2=“about half the time,” 50%; and 1=“less than half of the time,” <50%). Nonadherence is defined as those who answer 3 (“most of the time,” 75% or less).

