#### Medication Adherence—Medication Adherence Scale

Self-reported medication adherence data and estimations from dispensed medication possession ratios will be used, following methodology from previous studies on medication adherence [30,31]. It will assess compliance with medications over the preceding 3 months. The primary measure item asks how often participants took their medication as prescribed over the preceding 3 months. Nonadherence is defined as 75% of the time or less.

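### The follow-up nonadherence rule names only answer 3 although its own gloss means answers 1 to 3; once corrected, the CBT item still needs reading alongside fatigue

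*Protocol article*

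**What the plan says.** The Uptake and Adherence section of the protocol article sets two follow-up questions. For exercise: "In the past 3 months, how often did you do your exercises as prescribed". For CBT: "In the past 3 months, how often did you use any of the CBT strategies to manage your fatigue". The legend of Figure 1 gives the timing: "At the 6- and 12-month time points, participants will also be asked about adherence to exercise and cognitive behavioral therapy strategies".

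Both questions use one five-point scale. The upper part is "5=“all of the time,” 100%; 4=“nearly all of the time,” 90%; 3=“most of the time,” 75" per cent; the lower part is "2=“about half the time,” 50%; and 1=“less than half of the time,” <50" per cent. One cut-off then serves both questions: "Nonadherence is defined as those who answer 3". With the gloss that follows in the same sentence, it reads: "Nonadherence is defined as those who answer 3 (“most of the time,” 75% or less".

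The medication adherence section has a rule of the same kind, stated without an answer code: "Nonadherence is defined as 75% of the time or less".

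**The concern.** The definition gives an answer code and a percentage range that do not describe the same people. Answer 3 is one category, 75%. The range of 75% or less takes in three categories. An analyst programming from the form works with the numeric code, and a derivation that flags only code 3 would leave the two lowest answers outside the nonadherent group.

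Correcting the code exposes a second, smaller difficulty that concerns CBT only. The exercise question has a stated reference, namely what was prescribed. The CBT question has none: the article states no amount of strategy use for follow-up, and Experimental Design says only that participants are asked to practise the skills after each session. The question also takes for granted that there is fatigue to manage, and none of the five listed answers covers a participant who no longer needs the strategies. Reducing fatigue is what the programme is for, so such participants are to be expected.

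At stake is how sustained adherence at 6 and 12 months is reported and read. Significance and Clinical Implications says that all pilot findings will be reviewed when deciding whether to go on to a definitive trial.

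**Working it through.** The plan gives no figure to reproduce here, and no sample size, power or significance level depends on this rule. The check is a mapping of the five answers.

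**Step 1. Apply both parts of the definition to the scale** (Uptake and Adherence).

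| Answer | Share of time | Rule by number (answer = 3) | Rule by gloss (75% or less) |
|---|---|---|---|
| 5 | 100% | not flagged | not flagged |
| 4 | 90% | not flagged | not flagged |
| 3 | 75% | nonadherent | nonadherent |
| 2 | 50% | not flagged | nonadherent |
| 1 | <50% | not flagged | nonadherent |

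The number alone gives an incoherent order: the middle answer is nonadherent and the two answers below it are not. The gloss gives a coherent order and matches the medication rule. The intended set is therefore 1, 2 and 3.

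**Step 2. Size of the difference if the number were coded.** Let p1 to p5 be the shares giving each answer. The rule by number gives p3; the rule by gloss gives p1 + p2 + p3. The gap is p1 + p2. The article gives no distribution, so these spreads are assumptions:

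| Assumed p1/p2/p3/p4/p5 (%) | By number | By gloss | Gap (points) |
|---|---|---|---|
| 20/20/20/20/20 | 20% | 20+20+20 = 60% | 40 |
| 10/15/25/25/25 | 25% | 10+15+25 = 50% | 25 |
| 15/15/25/25/20 | 25% | 15+15+25 = 55% | 30 |
| 30/20/20/15/15 | 20% | 30+20+20 = 70% | 50 |

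**Step 3. The CBT question under the corrected rule** (answers 1 to 3 nonadherent).

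- Fatigue resolved, strategies rarely needed: the natural answer is 1, scored nonadherent.
- Fatigue resolved because the strategies are still in use: the answer is 4 or 5, not flagged.
- Fatigue persisting, strategies in constant use: the answer is 5, not flagged.

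The first record shows that the cut-off can mix lack of need with lack of adherence. The second shows that recovery need not lower the reported use.

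**Step 4. Consistency of the two points.** Under the rule by number, the recovered participant who answers 1 is not flagged. The CBT difficulty arises only under the rule by gloss. The two faults do not operate together; the second appears once the first has been corrected.

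**Step 5. Reach.** Primary Endpoints defines feasibility by session attendance (at least 3 of 4 for GET and for CBT) and acceptability by a CSQ-8 score of at least 24 at 3 months. Statistical Methods builds the 24-of-37 rule on the same criteria. Neither uses the follow-up questions.

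**The case against.** The strongest reply is that the sentence has to be read whole. Its parenthesis covers answers 1 and 2, the medication rule confirms the intent, and an analyst is unlikely to treat a user at 75% as nonadherent and one below 50% as adherent. That stands as to intent and makes this a wording slip. It does not remove the need to correct the slip, because the code and the range still conflict inside an operative definition.

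On CBT, the reply is that the article does not say how recovered participants answer, that the form itself is not shown, and that skills such as pacing or goal setting may continue after fatigue has improved. This largely stands. What remains is visible in the quoted question and its five answers: the premise of fatigue, the missing reference amount, and no answer for lack of need.

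A reader might infer that better results from the programme must lower reported CBT adherence, and might try to size this. If 20% to 40% recovered and all of them answered 1, with 30% of the rest nonadherent, the reported rate would be 0.20 + 0.80 × 0.30 = 44% to 0.40 + 0.60 × 0.30 = 58%, against 30%. The document supplies none of these inputs and does not establish the direction, so the figures only restate their assumptions.

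A reader might also infer that the feasibility assessment is compromised. It is not, because primary feasibility rests on session attendance. Every response category is recorded and FACIT-F is measured at the same visits, so nothing is lost beyond repair.

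**Conclusion.** The definition is wrong as written, and the fault is minor. It names one answer where its own gloss and the medication rule mean three. If the number were coded, nonadherence would be understated by the combined share of answers 1 and 2, which is 25 to 50 points under the assumed spreads above and unknown in fact.

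Under the corrected rule, a low CBT answer cannot by itself be read as nonadherence, because it may reflect fatigue that has resolved. This secondary point rests on the wording of the question and the listed answers. Its size and direction are not established.

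The effect is confined to follow-up adherence at 6 and 12 months. The coprimary endpoints and the 24-of-37 decision rule stand.

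**What to change.** 1. Reword the rule so that nonadherence is an answer of 3 or lower (1, 2 or 3), in line with the medication rule. This costs nothing and needs no change to the form.

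2. For CBT, report strategy use by response category alongside FACIT-F at 6 and 12 months, and do not interpret the 75% cut-off alone as CBT nonadherence. The cost is one extra table and a less simple summary figure. Both measures are already collected at those visits, so this also covers participants who have already answered. Recruitment began in July 2025, so the first recruits would have reached 6 months by early 2026.

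Adding a not-needed answer and removing those participants from the denominator is a less clean remedy. It would make the denominator depend on an outcome after randomisation, and it could not be applied to forms already completed.

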#### Willingness to Pay

Participants will be asked about their willingness to pay for the program, pegged to 5 different prices that reflect the varying levels of government subsidy for the private and subsidized tiers available in public hospitals in Singapore. This information can be used for planning future subvention requests for GET and CBT, or for implementation of the program extending beyond the scope of this study.

#### Fatigue—FACIT-F

The 13-item FACIT-Fatigue subscale assesses self-reported fatigue and its impact on activities of daily living and function [29], and is scored on a 5-point Likert-type scale with reference to the preceding week. It has been validated in patients with cancer aged 18 years and older. The FACIT-F score ranges from 0 to 52, with higher scores indicating less fatigue.

#### Medication Adherence—Medication Adherence Scale

Self-reported medication adherence data and estimations from dispensed medication possession ratios will be used, following methodology from previous studies on medication adherence [30,31]. It will assess compliance with medications over the preceding 3 months. The primary measure item asks how often participants took their medication as prescribed over the preceding 3 months. Nonadherence is defined as 75% of the time or less.

#### QoL—FACT-G

The FACIT-General is a 27-item questionnaire designed to measure 4 domains of health-related QoL in patients with cancer, namely physical, social, emotional, and functional well-being [32]. It is scored on a 5-point Likert-type scale with a recall period over the preceding week. This questionnaire has been well validated in patients with cancer aged 18 years or older. The FACT-G total score ranges from 0 to 108, with higher scores indicating better QoL. The total score is broken down into 4 subscales: physical (0‐28), social (0‐28), emotional (0‐24), and functional well-being (0‐28).

#### Physical and Functional Outcomes

##### GLTPAQ

The GLTPAQ is a simple, self-reported questionnaire that is widely used to measure the amount of physical activity that a participant engages in during a typical 7-day period, with information gathered on the number of times one engaged in mild, moderate, and strenuous activity [33].

##### 6MWT

The 6MWT is a self-paced, submaximal exercise test measuring the distance a participant can walk within 6 minutes (in meters), assessing their aerobic capacity and endurance. The distance walked within 6 minutes can also be used to compare changes in functional capability [34].

##### Handgrip Strength

HGS, measured with a handheld dynamometer, provides a surrogate measure of overall muscle strength and physical function [35]. Measurement position is standardized, with the participant seated and their elbows at 90°, and measurements will be done in triplicate on both arms, with the highest value recorded (in kilograms).

##### 5-Times Sit-to-Stand Test

The 5-times sit-to-stand test evaluates lower limb strength and dynamic balance and provides an indication of the risk of falls in an individual [36]. The participant begins seated on a chair (without armrests or wheels), with arms folded across their chest. They will stand fully upright and sit down again with their back fully against the backrest, as quickly as possible. The time taken to complete 5 repetitions is recorded (in seconds), with a lower time indicating a better outcome.

### Study-Specific Exploratory Items

In addition to the validated outcome measures described above, participants will be asked to complete study-specific patient feedback items.

Close-ended items assessing the perceived helpfulness of the intervention:

“To what degree did this program help you to better understand the overall experience of breast or gynecological cancer?”“To what degree did the program teach you skills that are helping you to better manage your symptoms?”

Responses will be recorded on a 4-point Likert scale, with higher scores indicating greater perceived helpfulness.

For participants assigned to the GET plus CBT arm, an additional close-ended categorical item will assess the use of CBT materials:

“Which version of the CBT handout did you find most useful?”

Participants will select 1 of the 4 response options: digital only, print only, both digital and print, or neither.

Two additional open-ended questions will invite participants to describe the most and least helpful parts of the program and provide suggestions for improvement.

### Expected Risks

There are no additional toxicities or adverse effects anticipated, given that participants who have consented to the study will continue to receive medical management in line with usual care, which includes exercise therapy by rehabilitation professionals. The CBT procedures in this study have been previously described without additional adverse effects. During the consent process, patients will be informed that their participation in this study is voluntary. Withdrawal from the study will not affect their treatment, care, or any benefits to which they are entitled. The consent process will be carried out in a quiet and conducive room as far as possible. Provisions for adverse event monitoring for both GET and CBT have been described above under the *Experimental Design* section. All participants may choose to withdraw from the study completely at any point in time.

As the study is considered minimal risk, the principal investigator is responsible for monitoring the data, assuring protocol compliance, and conducting safety reviews. During the review process, the principal investigator will evaluate whether the study should continue unchanged, require modification or amendment, or close to enrollment. A log of adverse events will be maintained by the study staff and reviewed on a regular basis by the principal investigator. Serious adverse events will be reported as per institutional review board guidance. Adverse events will be categorized and summarized by intervention arm using counts and proportions. The study protocol will be reviewed by the institutional review board. Protocol changes will be communicated to relevant parties via weekly team meetings and timely email communications.

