All analyses, except for safety data, will be based on an intention-to-treat approach. Safety data will be reported based on the actual intervention received by participants. Descriptive statistics will be used to summarize participants’ characteristics, the willingness-to-pay survey, safety data, and close-ended participant feedback items. Responses to open-ended questions will be analyzed using descriptive content analysis to identify common themes and illustrative examples. The primary feasibility endpoint will be estimated based on the exact method. The primary acceptability endpoint will be estimated based on a mixed effects logistic regression model. This model will include indicator variables for postbaseline assessment time points and study sites as fixed effects and patient-specific random intercepts. Continuous secondary outcome measures, including FACIT-F, Medication Adherence Scale, FACT-G, GLTPAQ, 6MWT, HGS, and 5-times sit-to-stand test, will be analyzed using mixed effects linear regression models for repeated measures. For each measure, the change in score between assessment time points within each arm and the difference in scores between the 2 arms at the various assessment time points will be estimated and reported with 95% CIs. Each mixed effects linear model will include study arm, indicator variables for postbaseline assessment time points, interaction terms between the time variables and study arm, and study sites as fixed effects and patient-specific random intercepts. Models estimating the difference in scores between the 2 arms at various assessment time points will be further adjusted for baseline score. The choice of the structure used to fit the covariance matrix of each mixed effects model will be assessed at the time of analysis. No imputation for missing data will be carried out, and all patients with nonmissing data at any one of the assessment time points will be included in the analysis. No adjustment for multiple comparisons of secondary outcome measures will be made.

Two sets of analyses will be conducted. The first set will be based on the primary study cohort, and the second set will be based on the combined primary and exploratory study cohorts. For the second set, no hypothesis testing will be conducted. The focus of this set is to generate outcome estimates in all patients with BC to facilitate future study planning.

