The main limitation that the team foresees would be technological challenges that may impede the delivery of GET and CBT interventions. These include factors such as Wi-Fi connectivity, access to appropriate technological equipment (eg, a device with a webcam), and sufficient technology literacy to operate them, which may be more significant in the lower educated or older populations. Another limitation is that this study is nonblinded and may be susceptible to various biases. Self-reported outcomes in the GET plus CBT arm can be distorted by patients who may report more positive outcomes due to their belief that CBT is effective in reducing their fatigue. To mitigate this expectation bias, objective outcome measures are used to supplement self-reported data for study endpoints, wherever feasible. For instance, adherence to BC treatments is estimated based on medication possession ratios, which are derived based on drug dispensing records, in addition to patients’ responses to the medication adherence survey form. To manage a patient’s expectations, it is highlighted in the patient information sheet that the investigators are not clear whether patients will derive benefit with the addition of CBT, given that there are limited studies on the effects of CBT on fatigue. To prevent performance bias, rehabilitation physicians prescribing exercise therapy are kept blinded to the study arm of each patient. To minimize detection bias, the recruiting research assistant who conducts all physical tests on patients will follow a standardized set of procedures. A further limitation is that participants in the GET and CBT arm receive additional therapist contact through CBT sessions, which is not provided in the GET-only arm. Consequently, any observed differences in outcomes between the 2 arms cannot be unequivocally attributed to the specific therapeutic components of CBT. A future definitive RCT could address this by incorporating an attention-control condition for the GET-only arm, thereby enabling clearer isolation of the specific effects of CBT from those related to increased therapist contact.

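### Adverse events are looked for through more routes in the GET plus CBT arm than in the GET-only arm, and the by-arm summary does not separate events by source (minor)

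*Protocol article*

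**What the plan says.** All places are in the protocol article.

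- **Routes in both arms (Experimental Design).** Three routes are listed for GET, which both arms receive: "Weekly phone calls are made by the study coordinator to check for the onset of any new symptoms, distress, or adverse events"; "Monthly video consultations with rehabilitation physicians"; and "An exercise diary with provisions for participants to record any adverse events". Adverse events are also passed to the clinical investigators for follow-up.
- **Route in one arm only (Experimental Design).** The GET plus CBT arm has four further one-hour sessions within 12 weeks. Of these it says: "The first 10 to 20 minutes at the start of each session are allocated to check on" participants' welfare and to go over skills already taught. High distress is assessed and triaged. Session 2 leaves time for sleep, mood and cognitive difficulties.
- **Status of that route (Expected Risks).** "Provisions for adverse event monitoring for both GET and CBT have been described above". The article thus regards the CBT provisions as adverse event monitoring.
- **Summary (Expected Risks; Statistical Methods).** Study staff keep a log. "Adverse events will be categorized and summarized by intervention arm using counts and proportions". Also, "Safety data will be reported based on the actual intervention received by participants". No formal between-arm testing is planned.
- **Acknowledged imbalance (Strengths and Limitations).** "participants in the GET and CBT arm receive additional therapist contact through CBT sessions, which is not provided in the GET-only arm". This is given as a limit on attributing differences in outcomes. Safety is not named.

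**The concern.** A by-arm table of adverse events in a randomised trial is read as a comparison even when no test accompanies it. That reading is sound only if events had the same chance of being recorded in each arm. Here one arm has an additional route, staffed by psychologists and directed at distress, mood and sleep. An excess in those categories could come from better detection and still look like a harm of CBT.

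Reporting by intervention received may tie the two together more closely. The participants counted under GET plus CBT would then presumably be those who attended CBT sessions, which are the contacts that add detection.

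The stakes are modest but real. The principal investigator reviews the log when judging whether the study continues unchanged, and all pilot findings feed the decision on a definitive trial.

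**Working it through.** The article gives no adverse event rate or detection rate, so there is no stated figure to reproduce. What follows only shows the order of size.

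**Inputs from the article**
- GET consultations: first session plus weeks 4, 8 and 12, so 4.
- CBT sessions: 4 within 12 weeks.
- Primary cohort: 45 per arm.

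**Assumptions**
- Weekly calls run for 12 weeks, so 12 calls.
- True risk is the same in both arms: 20% or 40% of participants have an event.
- An event stays reportable for m weeks (1, 4 or 12), and each contact in that time detects it with probability q.
- The diary is ignored. This overstates the imbalance, because both arms have it.

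**Contacts.** GET only: 12 + 4 = 16. GET plus CBT: 16 + 4 = 20, which is 4/16 = 25% more.

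**Equal detection per contact.** Detection is 1 − (1 − q)^(16m/12) with GET and 1 − (1 − q)^(20m/12) with GET plus CBT. The excess in recorded risk is the true risk times the difference.

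| q | m (weeks) | GET | GET plus CBT | Ratio | Excess at 20% risk (points) | Excess at 40% risk (points) |
|---|---|---|---|---|---|---|
| 0.2 | 1 | 0.257 | 0.311 | 1.207 | 1.1 | 2.1 |
| 0.2 | 4 | 0.696 | 0.774 | 1.113 | 1.6 | 3.1 |
| 0.2 | 12 | 0.972 | 0.988 | 1.017 | 0.3 | 0.7 |
| 0.5 | 1 | 0.603 | 0.685 | 1.136 | 1.6 | 3.3 |
| 0.5 | 4 | 0.975 | 0.990 | 1.015 | 0.3 | 0.6 |
| 0.8 | 1 | 0.883 | 0.932 | 1.055 | 1.0 | 1.9 |
| 0.95 | 1 | 0.982 | 0.993 | 1.012 | 0.2 | 0.5 |

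The table holds close to the worst case. With x = (1 − q)^m, the difference in detection is x^(4/3) − x^(5/3). It is largest at x^(1/3) = 0.8, where it equals 0.8^4 − 0.8^5 = 0.4096 − 0.3277 = 0.0819. Whatever q and m are, the excess cannot exceed 0.0819 times the true risk: 1.6 points at 20% and 3.3 points at 40%. The latter is 45 × 0.4 × 0.0819, or about 1.5 participants.

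**Chance error with 45 per arm.** The standard error of the difference is √(2p(1 − p)/45): 8.4 points at p = 0.20 and 10.3 points at p = 0.40.

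**Unequal detection.** Let CBT sessions detect with probability 0.8 and the shared contacts with a lower one. With one week reportable:
- Shared 0.5: 0.603 against 0.768, ratio 1.27 (3.3 points at 20% risk, 6.6 at 40%).
- Shared 0.3: 0.378 against 0.637, ratio 1.68.
- Shared 0.1: 0.131 against 0.492, ratio 3.75 (7.2 points at 20% risk, 14.4 at 40%).

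With four weeks reportable, the ratios are 1.02, 1.15 and 2.17.

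**The case against.** The strongest reply is that the shared monitoring is already dense. The weekly calls ask about distress by name in both arms, and physician consultations and a diary support them. An extra CBT contact matters only for an event that all of these miss. The summary is descriptive, the go/no-go rule does not use adverse events, and counts and proportions are a normal presentation. The article is also condensed, so the fields of the log may be set out elsewhere. Most of this stands, and it is why the point is minor. It does not remove the asymmetry, which the article states itself, and the limitation on extra contact does not mention safety. A bias smaller than chance error is still systematic.

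A reader might infer more than the document supports:

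- **That the GET plus CBT arm will show more events, by 6 to 8 points.** Such a gap arises if every contact independently brings out a new event. With a probability of 2%, 5% or 10% per contact, 1 − (1 − p)^16 against 1 − (1 − p)^20 gives 27.6% against 33.2%, 56.0% against 64.2%, or 81.5% against 87.8%. That model lets contacts create events and does not hold true risk equal. Even a real small excess could be reversed by chance.
- **That the fatigue tracking diary is another adverse event source.** The article describes it as part of CBT and does not name it as a source.
- **That distress in the GET-only arm has no onward route.** Adverse events go to the clinical investigators for follow-up. Who should be referred is clinical management and outside this point.
- **That referrals from CBT are an unrecorded co-treatment.** Nothing in the article says that they go unrecorded.

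**Conclusion.** The point holds as a minor one. Ascertainment of adverse events differs by arm, the planned summary makes no stated allowance for it, and any resulting bias would raise recorded events with GET plus CBT, chiefly distress, mood or sleep events.

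The direction follows from the article. The size does not, because it rests on assumed detection rates, assumed true risks of 20% to 40% and 12 weekly calls. It is probably small, at about 0 to 3 percentage points with equal detection per contact. A large distortion needs calls and consultations that detect very little beside CBT sessions that detect much more, which is hard to assume when the calls ask about distress. The fault is the unseparated source of the events. The use of counts and proportions is not at fault.

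**What to change.** 1. Add a source-of-report field to the existing adverse event log (weekly call, GET consultation, exercise diary, CBT session, other), unless the case report form already has one.
2. Keep the all-source by-arm table. Dropping it would hide any harm that CBT itself provokes.
3. Add a by-arm table restricted to the routes common to both arms: weekly calls, GET consultations and exercise diary. List separately the events found only at CBT sessions.
4. Extend the extra-contact limitation in Strengths and Limitations to the recording of adverse events.

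The cost is one log field, one more descriptive table with a short list, and one sentence. Recruitment stood at 48 at the end of April 2026, so events logged before the change may need their source coded from existing notes, and that may not be possible for all of them.
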